### 2c. Association between e-ASPECTS or e-CTA results and clinical outcome after stroke

We will use the entire RITeS samples of NECT and CTA for these analyses but also perform sensitivity analyses using the representative NECT sample.

In separate multivariable analyses, we will test whether the three main software outputs of e-ASPECTS (ASPECTS result) and e-CTA (ICA-MCA axis occlusion, MCA territory collateral score) are independently associated with stroke outcome. We will include the following variables in each model since these are already known to be associated with outcome after stroke: age, NIHSS, time from stroke onset, treatment with alteplase and/or thrombectomy (vs no treatment). The dependent variable in each model will be functional outcome after stroke. Assessment of functional outcome after stroke varies among the RITeS trials and includes either the modified Rankin Score (mRS) at 90 days, or the Oxford Handicap Scale (OHS) at 6 months from stroke onset. Both mRS and OHS are 7-point scalar ranging from normal (0) through increasing disability (1–5), to death (6). We will use multivariable ordinal logistic regression to calculate common odds ratios for good outcome, presented as per Table 10.

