### Inclusion and exclusion criteria

We will derive separate but overlapping samples for e-ASPECTS and e-CTA testing from all baseline scan data available to RITeS. We will produce a STARD-type (Standards for Reporting Diagnostic Accuracy Studies) flow chart^24^ to show reasons for inclusion/exclusion of cases and successful/non-successful scan assessment by human-readers and software for all patients available to RITeS.

**
*Sample for e-ASPECTS evaluation.*
** There are no precise data for the true case-mix of patients initially assessed for presumed stroke, and for whom hospital admission staff may decide to use e-ASPECTS and e-CTA software to assess treatment eligibility. Pooled data from the major thrombolysis and thrombectomy RCTs will be similar to the case-mix considered for these treatments but may include patients with more severe stroke than those seen in routine practice and will not include patients who present late^4^,^25^. Conversely, patients with haemorrhagic stroke are most likely to be severely affected by stroke symptoms^26^, and a proportion may be too sick to be appropriately represented in trials. The Sentinel Stroke National Audit Programme (SSNAP) provides routinely collected UK data for all patients ultimately diagnosed with stroke in England, Wales and Northern Ireland and includes many patients with minor symptoms or delayed/uncertain time of presentation who would not routinely be considered for thrombolysis or thrombectomy^27^. Importantly, all of these data sources only include patients after excluding structural stroke mimics. RIGHT-2 recruited patients at first contact with ambulance staff in the community and reported 26% stroke mimics^17^. A prospective single-centre study of patients with suspected stroke following stroke expert review after arrival at hospital found a similar proportion of mimics^28^. Additionally, in up to 7% of patients with stroke, it is only possible to obtain imaging of poor quality due to patient movement, beam hardening artefacts or variable patient orientation in the scanner, all of which may influence the performance of e-ASPECTS and e-CTA software^3^,^11^. Finally, the sensitivity and specificity of diagnostic tests may vary with prevalence^29^. 

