To derive a ‘real-world’ dataset from all patients available to RITeS, and simultaneously maximise sample size, we will therefore: 1) Include all structural stroke mimics for e-ASPECTS testing (since this will be far less than 26%, but see planned sensitivity analyses for our primary outcomes below)2)For the remainder of included patients (i.e. non-mimics), aim for sex and age mix, stroke severity and time since symptom onset similar to SSNAP, pooled thrombolysis/ thrombectomy RCT data, and haemorrhagic stroke registry data.3)Not exclude imaging based on quality.

The most recent SSNAP annual dataset (Apr 2018-Mar 2019) identified 87,635 patients presenting acutely with stroke and had 93% data completion. Of these patients, 47.8% were female, median age was 77 years, 87.1% of strokes were ischaemic, 12.4% were haemorrhagic (0.4% unknown), and the median NIHSS was 5. For 69.4% of patients, the time of symptom onset was known and the median time from stroke onset to baseline scan in these patients was 4 hours and 2 minutes^30^. A pooled analysis of nine thrombolysis RCTs by the Stroke Thrombolysis Trialists’ Collaborative (STTC) group included 6,756 patients of whom 45% were female, the mean age was 71 years, the mean NIHSS was 12, and the mean treatment delay was 4 hours^25^. A pooled analysis of seven thrombectomy RCTs by the Highly Effective Reperfusion evaluated in Multiple Endovascular Stroke Trials (HERMES) collaboration included 1764 patients of whom 47% were female, the median age was 67 years, the median NIHSS was 17, and the mean time from onset to randomisation was 3 hours^4^. A comprehensive, community-based audit of haemorrhagic stroke in Scotland (The Lothian Audit of the Treatment of Cerebral Haemorrhage, LATCH) included 137 patients with primary haemorrhagic stroke of whom 55% were female, the median age was 79 years, and the median Glasgow Coma Scale at presentation was 13^31^,^32^.

To ascertain the representativeness of the non-mimic cases within the RITeS dataset, we will report demographic and clinical data as per SSNAP, STTC, HERMES and LATCH data (see Table 2). We will report absolute differences, 95% confidence intervals and p-values for comparisons. We will also present continuous data components using overlapping histograms.

To ascertain the representativeness of relevant radiological features in RITeS, we will also report the features listed in Table 3.

**
*Sample for e-CTA evaluation.*

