### Tertiary outcomes

1. Difference in haemorrhage size and location results provided by e-ASPECTS versus expert human readers.2. Potential clinical impact of e-ASPECTS and e-CTA on routine acute stroke care, whether: a. knowledge of ASPECTS conveyed using e-ASPECTS visual overlay on imaging influences diagnostic confidence or alters treatment decisions,b. use of e-ASPECTS/e-CTA alter the time required for scan interpretation, andc. e-ASPECTS or e-CTA results are associated with outcome after ischaemic stroke.

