### Secondary outcomes

**
*1. e-ASPECTS processing success and factors influencing accuracy.*
** To present the most complete picture available, we will use the entire RITeS sample for these analyses (i.e. not just the representative sample) but we will also include a sensitivity analysis of the representative sample.

We will report the proportion of scans successfully and unsuccessfully processed by e-ASPECTS and collate reasons cited by e-ASPECTS for any processing failures. We will use summary statistics to describe and compare the subgroups of scans that were successfully versus unsuccessfully processed. This will include patient and radiological factors (see Table 4).

To determine the influence of patient and radiological factors on the accuracy of ASPECTS results produced by e-ASPECTS software, we will perform multivariable ordinal logistic regression using the variables pre-specified in Table 5. The dependent variable will be the absolute difference in ASPECTS between e-ASPECTS and expert human readers (i.e. scalar, 0-10).

For any variables found to be significantly associated with poorer e-ASPECTS results on regression testing (i.e. independently associated with greater difference between e-ASPECTS and expert human reader scores), we will also calculate and compare diagnostic accuracy figures (as above) for each of the subgroup arms (for these analyses only, continuous data will be dichotomised as per Table 5).

Finally, to account for (the as yet unknown) covariates that alter e-ASPECTS diagnostic accuracy figures, we will derive covariate-adjusted ROC curves (AROC)^50^.

**
*2. Identification of CTA obstruction and collateral scoring by e-CTA versus expert human readers.*
** There are two components to the e-CTA output: 1. Where ICA-MCA occlusion is identified, the location is categorised either proximal (ICA/proximal MCA) or distal (distal MCA). Other arteries are not assessed.2. MCA collateral scoring (modified Tan *et. al*. 2009)^51^ is given for all cases on the scale 0 = no collaterals (<10% of affected MCA territory compared to contralateral side), 1 = poor (10–50%), 2 = good (50–90%), 3 = excellent (>90%) collaterals (i.e. includes normal scans).

The expert human rated CTAs available to RITeS include similar scoring methods for comparison with e-CTA outputs, but also additional measures such as degree of arterial patency (i.e. from fully patent through increasingly obstructed to occluded)^22^.

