**Table 3. T3:** Planned assessment of radiological characteristics of the entire RITeS dataset.

Radiological Finding		N (%) or Median (IQR)
Ischaemic brain changes	None	
	Subtle (e.g. loss of grey-white margins)	
	Obvious (e.g. hypoattenuation relative to normal white matter +/- swelling)	
Ischaemic location	MCA territory	
	Other cerebral	
	Brainstem or cerebellum	
	Cortical	
	Subcortical	
Hyperattenuating arteries	List location	
Haemorrhage location	Deep	
	Lobar	
	Intraventricular	
	Extra-axial	
Structural stroke mimic	List type (e.g. tumour, inflammation, collection)	
Pre-stroke brain changes	Atrophy	
	Leukoaraiosis	
	Old Stroke lesions	
CT slice thickness	Thin (≤ 1 mm)	
	Medium (> 1 mm ≤ 5 mm)	
	Thick (> 5 mm)	

**Table 4. T4:** Planned univariable comparison of scans successfully versus unsuccessfully processed by e-ASPECTS.

Variable	Successfully Processed	Not Successfully Processed	Absolute differences, 95% CI and p-value
Patient age (median, IQR)			
Patient sex (n, %)			
Minutes from stroke onset to scan (median, IQR)			
NIHSS (median, IQR)			
Stroke aetiology (n, %): • Ischaemia MCA territory • Ischaemia elsewhere • Haemorrhage • Mimic			
Presence of pre-stroke brain changes (n, %): • Atrophy • Leukoaraiosis • Old stroke lesions			
CT slice thickness (n, %): • ≤ 1 mm • > 1 mm ≤ 5 mm • > 5 mm			
Image quality (n, %): • Good quality • Movement artefacts • Streak artefacts • Patient malposition			

Note: IQR = Inter-quartile range. MCA = middle cerebral artery. NIHSS = National Institutes of Health Stroke Scale.

**Table 5. T5:** Variables for multivariable analysis and subgroups for diagnostic accuracy testing.

Clinical Characteristics		Imaging Findings		Imaging Technique	
Age	≤60 years	ASPECTS	<6	CT slice thickness	≤1 mm
	>60 years		≥6		> 1 mm
NIHSS	0–6	Infarct Location	MCA territory	Poor patient positioning	Yes No
	7–12		Elsewhere		
	>12	Atrophy, Leukoaraiosis, Old stroke lesion	Yes No		
Time from stroke onset to scan	<3 hours				
	3+ hours			Imaging artefact (movement or streak)	
Knowledge of affected side	Yes No				

**Table 6. T6:** Comparison of ICA-MCA axis occlusion identified by e-CTA and expert-human groups.

Human Readers e-CTA	Proximal Occlusion	Distal Occlusion	TOTAL
Proximal Occlusion			
Distal Occlusion			

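### Tertiary outcome 2c is defined for ischaemic stroke but analysed without that restriction, and its single treatment term leaves part of any thrombectomy effect in the e-CTA occlusion odds ratio

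*SAP article*

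**What the plan says.** Under Tertiary outcomes, item 2c is whether "e-ASPECTS or e-CTA results are associated with outcome after ischaemic stroke". The analysis section has a wider title, "Association between e-ASPECTS or e-CTA results and clinical outcome after stroke", and a wider sample: "We will use the entire RITeS samples of NECT and CTA for these analyses". A sensitivity analysis in the representative NECT sample is added. No sentence in the section excludes mimics or haemorrhage.

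Elsewhere in the article, the word entire marks the full pool. For secondary outcome 1 the plan writes "we will use the entire RITeS sample for these analyses (i.e. not just the representative sample". Table 3, titled "Planned assessment of radiological characteristics of the entire RITeS dataset", has rows for haemorrhage and for structural mimics.

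Each 2c model is an ordinal logistic regression of mRS or OHS on one software result, adjusted for age, NIHSS, time from onset and a single treatment term: "treatment with alteplase and/or thrombectomy (vs no treatment". Table 10 also gives treatment one row, but words it as alteplase with or without thrombectomy.

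**The concern.** There are two separate defects.

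- **Population.** The outcome definition and the analysis section name different populations. If non-ischaemic cases stay in the model, the ASPECTS odds ratio mixes prognosis within ischaemic stroke with the contrast between ischaemic stroke and other diagnoses.
- **Treatment coding.** The section aims at an independent association and adjusts for treatment to reach it. The term as coded cannot separate alteplase plus thrombectomy from alteplase alone. Thrombectomy is given for arterial occlusion, which is the exposure in one of the three models, so the adjustment is incomplete where it matters most.

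At stake is the interpretation of two tertiary odds ratios, to be reported after the primary publication.

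**Working it through.** **Pool.** The Table 1 counts sum to 104 + 98 + 3035 + 947 + 65 + 113 + 271 + 537 + 1149 + 293 = 6612, which agrees with the stated total of over 6600. The haemorrhage studies (LINCHPIN, RESTART) contribute 947 + 537 = 1484, or 22.4%. The ischaemic-type studies contribute 6612 − 1484 = 5128.

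**Who could enter the 2c model.**

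- *Haemorrhage studies.* The article gives GCS as the severity measure for haemorrhagic stroke, the model needs NIHSS, and nothing is imputed. Table 1 lists follow-up as post-mortem (LINCHPIN) and 1–3 years (RESTART), whereas 2c uses outcome at 90 days or 6 months. Most of these 1484 would probably drop out, but through missing data and not by a stated rule.
- *Non-ischaemic cases inside ischaemic-type studies.* RIGHT-2 "reported 26% stroke mimics": 0.26 × 1149 = 299, which is 299/5128 = 5.8%. This is an upper guide. The 26% covers all mimics, the article expects structural mimics to be far fewer, and it does not say that NIHSS was recorded for mimics.
- *Sensitivity analysis.* It does not remove mimics, because the representative sample is built to "Include all structural stroke mimics for e-ASPECTS testing".

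**Possible size for the ASPECTS model.** To first order, with mimic share p, a gap d in mean software ASPECTS (mimics minus the rest), score variance V and a gap δ in the log-odds of good outcome, the log odds ratio per point shifts by about p(1 − p) × d/V × δ. Take p = 0.058 (the upper guide) and assume V = 5, d = ±1.2 and δ = 0.7 to 1.5:

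- 0.058 × 0.942 × 1.2/5 = 0.0131
- × 0.7 = 0.009 and × 1.5 = 0.020
- a true odds ratio of 1.00 becomes 1.01 to 1.02 if d is positive, and 0.98 to 0.99 if d is negative.

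The sign follows d, and the Introduction says it is unclear how the software handles other pathologies.

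**Treatment term.** In PISTE both arms had alteplase and one also had thrombectomy. The any-versus-none term is 1 for all 65 patients and cannot carry that contrast.

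**CTA pool from Table 1.** IST-3 about 270, PISTE 65, PRACTISE 0.5 × 271 = 135.5, SITS Open 0.05 × 293 = 14.65: about 485 in total (about 598 if all 113 POSH patients count).

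**Thrombectomy share among occluded patients.** Assume 40% occlusion in IST-3 and PRACTISE, no thrombectomy there, all PISTE and SITS Open CTA patients occluded, and half of those treated:

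- occluded: 0.4 × (270 + 135.5) + 65 + 14.65 = 241.85
- thrombectomy: (65 + 14.65)/2 = 39.8
- share: 39.8/241.85 = 16%, and 39.8/485 = 8% of the pool.

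If 60% of occluded PRACTISE patients had thrombectomy, the share rises to about 30%.

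**Shift in the occlusion odds ratio.** With no thrombectomy in non-occluded patients, the factor is roughly OR^share:

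| Share of occluded | OR 1.5 | OR 2.5 |
|---|---|---|
| 10% | 1.04 | 1.10 |
| 16% | 1.07 | 1.16 |
| 30% | 1.13 | 1.32 |

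A large-sample proportional-odds simulation of this CTA pool took a true occlusion odds ratio of 0.50, alteplase 1.3 and thrombectomy 1.5 to 2.5. The merged term gave 0.54 to 0.65. Separate terms gave 0.49 to 0.53, and that spread is simulation noise. In every scenario the merged estimate moved toward 1.

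**Wording.** Section 2c counts thrombectomy alone as treated. The Table 10 row does not clearly cover it. The clinical-impact questionnaire (2a) offers thrombectomy without alteplase as a choice, so the plan recognises that category.

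**The case against.** The phrase about entire samples can be read as naming the data pool, in contrast to the representative subsample, with the population already fixed by the outcome list. Section 2c also speaks of outcome after stroke, and a mimic is not a stroke. That reading is possible and would make this a clarification. It does not settle the matter: nothing in 2c applies the restriction, the same phrase elsewhere covers mimics and haemorrhage, and haemorrhage is stroke in any case.

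A reader might infer that 299 mimics, or the whole of the haemorrhage cohorts, will enter and inflate the ASPECTS odds ratio. The documents do not support that. The 299 is an upper guide, most haemorrhage cases probably fall out for want of NIHSS, and neither the software scores nor the prognosis of mimics is given.

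On treatment, one can argue that 2c concerns association and not causation, that few CTA patients had thrombectomy, and that a separate term would be imprecise and tied to occlusion. The imprecision is real. Collinearity is not a serious obstacle. With occlusion in half of the pool (241.85/485 = 0.499) and thrombectomy in 8.2%, all of it among the occluded, the squared correlation is 0.082 × 0.501/(0.499 × 0.918) = 0.09. The variance inflation is 1/(1 − 0.09) = 1.10, before other covariates and far below the plan's limit of 5.

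**Conclusion.** Both defects stand, as minor points on a tertiary outcome. The population in 2c is stated in two ways, and non-ischaemic cases are filtered only by whichever covariates happen to be missing. Any resulting bias in the ASPECTS odds ratio is of unknown direction and probably small.

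The merged treatment term leaves part of any thrombectomy effect in the occlusion odds ratio and, if thrombectomy helps, pulls it toward 1. The size is a factor of about 1.04 to 1.3. The top of that range needs both a 30% thrombectomy share and an odds ratio of 2.5, neither of which is documented. What Table 1 lets one place, about 16%, gives 1.07 to 1.16. These figures treat e-CTA occlusion as true occlusion; misclassification by the software would weaken the link.

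It would be too strong to conclude that the occlusion result is invalid or that the whole thrombectomy effect sits in it. The primary and secondary conclusions do not depend on this.

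**What to change.** - In section 2c, restrict the analysis to patients with a final diagnosis of ischaemic stroke, matching the outcome list, and apply the same restriction to the sensitivity analysis.
- Replace the single treatment term with two covariates, alteplase (yes/no) and thrombectomy (yes/no).
- Give Table 10 two matching rows, which also settles the coding of thrombectomy without alteplase.

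The change is to wording and should be made before unblinding. It costs somewhat fewer patients in the NECT model (the RIGHT-2 mimics would be at most about 299, plus any haemorrhages inside the ischaemic-type studies) and one more degree of freedom. The thrombectomy term will be imprecise, resting on roughly 40 of 485 CTA patients under the assumptions above, so it should be presented as an adjustment and not as an estimate of treatment effect.

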### Future data availability

In general, clinical imaging data in DICOM format are difficult to fully anonymise and are not routinely available for open sharing. Other clinical trial data may be available.

When RITeS data become available, these will be included here:

https://datashare.is.ed.ac.uk/handle/10283/3105. Some of the individual trial data are separately available as follows: IST-3 - https://datashare.is.ed.ac.uk/handle/10283/1931; RESTART - https://datashare.is.ed.ac.uk/handle/10283/3265.

## Conclusions

RITeS will provide robust but fair independent testing of e-ASPECTS and e-CTA software from Brainomix measured against the current gold standard for CT imaging assessment, expert-human interpretation.

This statistical analysis plan pre-specifies all methods prior to un-blinding and analysis of RITeS data.

## Data availability

### Underlying data

No underlying data are associated with this article.

### Reporting guidelines

Edinburgh Datashare: Statistical Analysis Plan checklist for ‘ Real-world Independent Testing of e-ASPECTS Software (RITeS): statistical analysis plan’. https://doi.org/10.7488/ds/2803^55^.

The completed reporting guidelines checklist is available under the terms of the Creative Commons Attribution 4.0 International license (CC-BY 4.0).

## Figures and Tables

**Table 1. T1:** Clinical stroke trials with baseline CT scans available for inclusion in RITeS.

Stroke Trial	Number patients	Baseline CT Assessment	Stroke Type	Trial Type	Other Scans	Follow-up Data
ATTEST	104	ASPECTS	Isch	RCT – IV alteplase or tenecteplase	CT at 24–48 hrs	2 & 90 days
EuroHyp	98	As per IST-3, excluding CTA.	Isch	RCT – systemic cooling to 34-5°C for 24 hours or control	CT/MRI at day 5	0–7 & 90 days
IST-3	3035	Ischaemia extent & location, ASPECTS, swelling, atrophy, leukoaraiosis, old stroke lesions, arterial patency & collateral scores on CTA, scan quality 3.	Isch	RCT – IV alteplase or control	Baseline CTA (in ~270) CT/MRI at 24–48 hrs	7 days & 6- months
LINCHPIN	947 *	Location & size of intracerebral haemorrhage	Haem	Observational cohort study	MRI at 3 months	Post-mortem
PISTE	65	As per IST-3.	Isch	RCT – IV alteplase and thrombectomy or IV alteplase alone	Baseline CTA CT/MRI at 22–36 hrs	2 & 90 days
POSH	113	Ischaemia volume on CT, ASPECTS, arterial patency on CTA	Isch	Observational study	CT at 24–48 hrs	
PRACTISE	271	As per IST-3.	Isch	RCT – Multimodal CT imaging (CT + CTA + CTP) or CT alone	Baseline CTA (in 50%) CT/MRI at 24 hrs	1, 7 & 90 days
RESTART	537	Location & size of haemorrhage, atrophy, leukoaraiosis, old stroke lesions, scan quality	Haem	RCT – restart or avoid antiplatelets after haem stroke	MRI pre- randomization (in 550)	1–3 years
RIGHT-2	1149	As per IST-3.	Isch	RCT – ultra-early transdermal GTN or control	CT at 24–48 hrs	4 & 90 days, 1 year
SITS Open	293	ASPECTS, swelling, arterial patency on CTA	Isch	Controlled study -thrombectomy vs control	Baseline CTA (in ~5%) CT/MRI at 22–36 hrs	1, 7 & 90 days

* Ongoing at time of data collection.

**Table 2. T2:** Planned assessment of demographic and clinical data for non-stroke mimic cases within the RITeS dataset, and comparison with other datasets.

Clinical Feature		RITeS dataset	SSNAP dataset	STTC dataset	HERMES dataset	LATCH dataset
Total patient number			87,635	6,756	1,764	137
Female sex			48%	45%	47%	55%
Age, years			77 (66-85)	71 (13)	67 (57-76)	79 (67-83)
Aetiology	Ischaemia		87%	100%	100%	-
	Haemorrhage		12%	-	-	100%
NIH Stroke Scale			5 (2-11)	12 (7)	17 (13-21)	-
Glasgow Coma Scale			-	-	-	13 (9-15)
Time from stroke onset, hours			4 (2-11)	4 (1.2)	3 (2-4)	-

Note: Data are percentage, median (inter-quartile range), or mean (standard deviation) as appropriate.

**Table 3. T3:** Planned assessment of radiological characteristics of the entire RITeS dataset.

Radiological Finding		N (%) or Median (IQR)
Ischaemic brain changes	None	
	Subtle (e.g. loss of grey-white margins)	
	Obvious (e.g. hypoattenuation relative to normal white matter +/- swelling)	
Ischaemic location	MCA territory	
	Other cerebral	
	Brainstem or cerebellum	
	Cortical	
	Subcortical	
Hyperattenuating arteries	List location	
Haemorrhage location	Deep	
	Lobar	
	Intraventricular	
	Extra-axial	
Structural stroke mimic	List type (e.g. tumour, inflammation, collection)	
Pre-stroke brain changes	Atrophy	
	Leukoaraiosis	
	Old Stroke lesions	
CT slice thickness	Thin (≤ 1 mm)	
	Medium (> 1 mm ≤ 5 mm)	
	Thick (> 5 mm)	

**Table 4. T4:** Planned univariable comparison of scans successfully versus unsuccessfully processed by e-ASPECTS.

Variable	Successfully Processed	Not Successfully Processed	Absolute differences, 95% CI and p-value
Patient age (median, IQR)			
Patient sex (n, %)			
Minutes from stroke onset to scan (median, IQR)			
NIHSS (median, IQR)			
Stroke aetiology (n, %): • Ischaemia MCA territory • Ischaemia elsewhere • Haemorrhage • Mimic			
Presence of pre-stroke brain changes (n, %): • Atrophy • Leukoaraiosis • Old stroke lesions			
CT slice thickness (n, %): • ≤ 1 mm • > 1 mm ≤ 5 mm • > 5 mm			
Image quality (n, %): • Good quality • Movement artefacts • Streak artefacts • Patient malposition			

Note: IQR = Inter-quartile range. MCA = middle cerebral artery. NIHSS = National Institutes of Health Stroke Scale.

**Table 5. T5:** Variables for multivariable analysis and subgroups for diagnostic accuracy testing.

Clinical Characteristics		Imaging Findings		Imaging Technique	
Age	≤60 years	ASPECTS	<6	CT slice thickness	≤1 mm
	>60 years		≥6		> 1 mm
NIHSS	0–6	Infarct Location	MCA territory	Poor patient positioning	Yes No
	7–12		Elsewhere		
	>12	Atrophy, Leukoaraiosis, Old stroke lesion	Yes No		
Time from stroke onset to scan	<3 hours				
	3+ hours			Imaging artefact (movement or streak)	
Knowledge of affected side	Yes No				

**Table 6. T6:** Comparison of ICA-MCA axis occlusion identified by e-CTA and expert-human groups.

Human Readers e-CTA	Proximal Occlusion	Distal Occlusion	TOTAL
Proximal Occlusion			
Distal Occlusion			
